## Statistical analysis

3

### Relationship between biomarkers and clinical findings

3.1

To evaluate the primary and secondary endpoints, we will conduct 2 statistical procedures. First, we will check the distribution of the primary EASI and all secondary clinical findings (POEM, Pruritus-NRS, Skin Comfort-NRS, and Treatment Satisfaction-NRS). The primary EASI and all secondary subjective scores will be logarithmically transformed, and whether the data are normally distributed will be checked. “% change from baseline of EASI and all secondary clinical findings at 16w” will be referred to as the dependent variable, whereas “baseline level of each of the 18 biomarkers” will be referred to as the independent variable.

If we can assume that the data on the log-transformed endpoints at 16w are normally distributed, we will use an analysis of covariance model, adjusting for confounding factors. As potential confounding factors, sex, age, and medical and family history will be included in the model because these are known as important risk factors for AD.

If the data for the log-transformed endpoints at 16w do not fulfil the assumption of normality, we will use generalized linear models, adjusting for confounding factors such as sex, age, and medical and family history.

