**Methods::**

Patients are at least 18 years of age and have moderate-to-severe AD with Eczema Area and Severity Index (EASI) ≥16, Investigator's Global Assessment ≥3, and body surface area ≥10%. We are going to enroll more than 130 subjects from 18 medical facilities. Clinical objective findings will be evaluated by EASI. Subjective symptoms will be assessed by Patient-Oriented Eczema Measure, Numerical Rating Scale for Pruritus (Pruritus-NRS), Skin Comfort-NRS, and Treatment Satisfaction-NRS. We will measure 18 blood/serum biomarkers including % eosinophils in blood cell count, lactate dehydrogenase, total IgE, soluble interleukin 2 receptor, CCL17, CCL18, CCL22, CCL26, CCL27, IL-13, IL-22, IL-24, IL-25, IL-31, IL-33, thymic stromal lymphopoietin, periostin, and squamous cell carcinoma antigen-2. The clinical evaluation and biomarker sampling will be performed at 0, 2, 4, 8, and 16 weeks of dupilumab treatment. We will also perform proteomic analysis (of roughly 300 proteins) of the patients’ sera obtained at 0 and 2 weeks of treatment. The primary endpoint is the association between “baseline levels of 18 biomarkers” and “% change from baseline of EASI at 16 weeks of dupilumab treatment.”

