### Study design

2.2

This is a multi-center, prospective, observational study in which samples/information will be obtained in Japan. This exploratory study will basically be carried out under real-world standard treatment guidelines. We are going to enroll more than 130 subjects from 19 medical facilities joining a consortium. The patients are to cease oral immunosuppressive drugs, oral steroids, or phototherapy at least 1 week before the start of injections of dupilumab. None of the patients is to have any previous experience of dupilumab treatment. They are to be at least 18 years of age, have moderate-to-severe AD with Eczema Area and Severity Index (EASI) ≥16, Investigator's Global Assessment (IGA) ≥3, and body surface area ≥10%, and be individuals for whom topical treatment of steroids provided inadequate control or was medically inadvisable, and had chronic AD for at least 3 years before the start of this study. The use of systemic steroids, systemic calcineurin inhibitors, and phototherapy is not allowed after the initiation of dupilumab.

The continued use of topical steroids, topical calcineurin inhibitors, topical moisturizers, and oral antihistamines used at baseline is allowed. Change of topical drugs to more potent ones is not allowed. The use of ocular, intranasal, or inhalant steroids and calcineurin inhibitors is allowed throughout the study, as is the use of anti-histamine drugs. Subjects are to receive subcutaneous injections of dupilumab (initial dose 600 mg, then 300 mg) biweekly for 16 weeks.

All investigators involved in this study shall carry out this study in accordance with the latest editions of the Declaration of Helsinki and “Ethical Guidelines for Medical and Health Research involving Human Subjects” of the Ministry of Health, Labour and Welfare, Japan. The study protocol has been approved by the Clinical Research Network Fukuoka Certified Review Board (CRB7180004). This study has been registered with the University Hospital Medical Information Network Clinical Trials Registry (UMIN000037307). The enrollment period is set to run from October 10, 2019. Last follow-ep date will be set on September 30, 2021.

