### Sample size estimates

2.3

The target number of 130 patients aimed to be enrolled was determined based on past experiences and feasibility. From previous phase 3 trials,^[7]^ since it is assumed that approximately 25% of enrolled patients with dupilumab treatment will discontinue the treatment, a plan was set to enroll more than 130 subjects and perform data analysis of at least 100 subjects.

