### Evaluation of clinical findings and biomarkers

2.5

Clinical objective findings are evaluated by EASI.^[42–44]^ Subjective symptoms are assessed by Patient-Oriented Eczema Measure (POEM)^[44,45]^ and Numerical Rating Scale for Pruritus (Pruritus-NRS) (Fig. 1).^[46,47]^ Patients are also requested to complete Skin Comfort-NRS (0: no discomfort, 10: worst discomfort imaginable) and Treatment Satisfaction-NRS (0: not satisfied at all, 10: very satisfied) (Fig. 1). We measure 18 biomarkers including % eosinophils in blood cell count, LDH, total IgE, soluble interleukin 2 receptor, CCL17, CCL18, CCL22, CCL26, CCL27, IL-13, IL-22, IL-24, IL-25, IL-31, IL-33, TSLP, periostin, and SCCA2. The clinical evaluation and biomarker sampling are performed on the day that injections of dupilumab start and at 2, 4, 8, and 16 weeks (w) of dupilumab treatment (Fig. 2). We also perform proteomic analysis (of roughly 300 proteins) (Myriad RBM, Austin, TX) of the patients’ sera on the day that injections of dupilumab start and at 2w of treatment.

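### The stated marker models leave out centre in an 18- or 19-centre study, so any centre differences shared by marker and outcome could bias or mask an association

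*Protocol article*

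**What the plan says.** Section 2.2 of the Protocol article describes the design: "This is a multi-center, prospective, observational study in which samples/information will be obtained in Japan". It puts the number of sites at 19: "We are going to enroll more than 130 subjects from 19 medical facilities joining a consortium". The Abstract says 18: "We are going to enroll more than 130 subjects from 18 medical facilities".

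The primary endpoint (section 2.6) relates 18 baseline markers to percentage change in EASI at week 16. For the analysis of covariance, section 3.1 states: "As potential confounding factors, sex, age, and medical and family history will be included in the model". The reason given is that these are risk factors for AD. If normality fails, a generalized linear model is used, and there the same factors are introduced as examples. Section 3.2 applies the same analysis to the roughly 300 proteins. Section 3.3 repeats the factors, again as examples, for the combined scores.

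No section names centre as a covariate, random effect, stratum or cluster.

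**The concern.** The listed factors were chosen because they raise the risk of having AD. Every patient here already has AD. What confounds the marker-response relation is something related to both baseline marker level and improvement, and centre is a plausible candidate. Section 2.2 places the study in routine care and lets patients continue their baseline topical drugs and antihistamines, so background treatment and case mix may differ between facilities. On outcome assessment, section 2.5 says only "Clinical objective findings are evaluated by EASI" and mentions no central rater. No randomisation or comparator balances such differences.

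If centre is related to both sides, a model without it can show an association that does not exist within centres, or hide one that does. The distortion can differ from marker to marker. That matters for a study whose aim is to find which marker is most strongly associated with improvement, because the ranking can shift as well as single p-values.

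**Working it through.** **Inputs from the documents.** 18 or 19 centres (Abstract; section 2.2). Section 2.3 gives more than 130 enrolled, a target set on this basis: "The target number of 130 patients aimed to be enrolled was determined based on past experiences and feasibility". It assumes that "approximately 25% of enrolled patients with dupilumab treatment will discontinue the treatment" and plans to "perform data analysis of at least 100 subjects".

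**The plan's own figure.** 130 × (1 − 0.25) = 97.5, close to the stated 100. Conversely 100 / 0.75 = 133.3, so 134, which fits an enrolment of more than 130. The figure of 100 is used below.

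**Patients per centre.** Analysed: 100/18 = 5.6 or 100/19 = 5.3. Enrolled: 130/18 = 7.2 or 130/19 = 6.8.

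**Assumptions, because the documents give no value.** A two-sided 5% level; the share of variance due to centre (ICC) in marker and in outcome; and the correlation ρ between a centre's effect on the marker and its effect on the outcome. The other covariates are left out of the simulated model.

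**Approximate formulas.**
- Bias in the correlation ≈ ρ × √(ICC_marker × ICC_outcome). For ICC 0.1 in both and ρ = 0.5: 0.5 × 0.1 = 0.05. For ICC 0.2 and ρ = 0.5: 0.5 × 0.2 = 0.10.
- Standard error inflation ≈ √(1 + (m − 1) × ICC_marker × ICC_outcome), with m = 5.26. For ICC 0.1: √(1 + 4.26 × 0.01) = 1.021. For ICC 0.2: √(1 + 4.26 × 0.04) = 1.082.

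With so few patients per centre, understated standard errors are a small matter. Bias from correlated centre effects is the larger one.

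**False-positive rate, no true within-centre association** (n = 100; 18 equal, 19 equal or 19 unequal centres; 3,000 runs per setting; Monte Carlo standard error near 5% is √(0.05 × 0.95/3000) = 0.4 points):

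| Assumed centre effects | Centre omitted | Centre as fixed effect |
|---|---|---|
| Outcome only, ICC 0.1 | 4-6% | 4-6% |
| ICC 0.05 in both, ρ = 0 | 5-6% | 5-6% |
| ICC 0.1 in both, ρ = 0 | 5-6% | about 5% |
| ICC 0.2 in both, ρ = 0 | 7-9% | 5-6% |
| ICC 0.1 in both, ρ = 0.5 | about 8% | 4-5% |
| ICC 0.2 in both, ρ = 0.5 | 17-19% | about 5% |

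**Masking, true within-centre correlation 0.3** (19 unequal centres):

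| Assumed centre effects | Power, centre omitted | Power, centre fixed |
|---|---|---|
| None | 86% | 80% |
| ICC 0.1 in both, ρ = 0 | 77% | 81% |
| ICC 0.2 in both, ρ = 0 | 68% | 80% |
| ICC 0.1 in both, ρ = −0.5 | 61% | 80% |
| ICC 0.2 in both, ρ = −0.5 | 37% | 80% |

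**Random centre intercept** (separate simulation, 19 unequal centres, 2,000 runs). The false-positive rate is 5-8% over ICC 0.05-0.1 with ρ = 0, ICC 0.1 with ρ = 0.5 and ICC 0.2 with ρ = 0.5. Without centre, the same runs gave 5-6%, 8% and 17%. With no centre effect, power for a correlation of 0.3 goes from 87.6% to 87.4%.

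**Clustered standard errors on the unsplit slope** (19 unequal centres, 3,000 runs). At ICC 0.2 and ρ = 0.5 the false-positive rate is about 15%, against 18% with no correction in the same runs. Clustering adjusts precision and leaves the between-centre bias in the slope.

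**The case against.** The strongest reply is one of scope. This is a condensed article, its SAP is not shown, and centre handling is often settled there. The generalized linear model and score passages give the factors only as examples, so centre could be added without contradiction. That stands for those passages. The covariance-model sentence is more definite: it says which factors go in and why, and the reason does not lead to centre. The point is therefore about the model as stated, not about missing detail.

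A reader might infer that centres are known to differ in EASI scoring, case mix or sample handling. The documents do not say so. They do not state who scores EASI, how samples are handled or where the 18 markers are assayed, and for the proteomic panel they name one laboratory. Common entry thresholds, central enrolment, independent monitoring and the bar on stronger topical drugs all limit variation.

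The rater mechanism is also narrow. A scoring difference that is proportional and constant over time at a centre cancels in percentage change; additive differences and drift do not. Eight of the nine secondary endpoints use patient-reported scores, which rater differences cannot explain. Case mix and co-treatment could still affect them.

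Finally, the study is exploratory and states no 5% threshold. That lowers the stakes for any single p-value, but not for the ranking of markers.

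**Conclusion.** The point holds in a limited form. The stated model omits centre in a multi-centre observational study, and this can bias or mask marker associations if centres differ on both marker and outcome. With modest, uncorrelated centre effects (ICC 0.05-0.1) the harm is close to nil: about 5-6% false positives. It becomes visible at ICC 0.1 with centre correlation 0.5 (about 8%) and substantial at ICC 0.2 with correlation 0.5 (17-19%). These inputs are assumptions, and nothing in the documents shows which setting applies.

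Two stronger conclusions are tempting and unsupported. One is that the planned standard errors are too small in general: when only the outcome varies by centre, the error rate stays at 4-6%. The other is that the upper figures are what this study should expect. They need sizeable centre effects on both sides and a correlation between them.

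The 18 versus 19 discrepancy needs correcting, but it is a separate matter and adds no weight here. Overall this is a minor, inexpensive improvement.

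**What to change.** Add centre as a random intercept to the models in sections 3.1 to 3.3. As a sensitivity analysis, report the within-centre slope, either by splitting the marker into its centre mean and the deviation from it or by fitting centre as a fixed effect. The random intercept alone reduces between-centre bias without fully removing it, so a clear gap between the two slopes would be a warning. If the mixed model does not converge, use centre fixed effects rather than clustered standard errors on the unsplit slope. State one number of facilities throughout.

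The cost is a sentence or two of text and no new data, since each patient's facility should be known from enrolment. The random intercept loses almost no power (87.6% to 87.4%). The within-centre analysis loses about 6-7 points if centres do not differ (86% to 80% with fixed effects), which is why it is better kept as a sensitivity analysis than made the main result.

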### Relationship between potential proteomic markers and clinical findings

3.2

To evaluate the association between “baseline level of each potential proteomic marker” and “% change from baseline of primary (EASI) and all secondary clinical findings (POEM, Pruritus-NRS, Skin Comfort-NRS, and Treatment Satisfaction-NRS) at 16w,” we will also check the distribution of the primary EASI and all secondary clinical findings as mentioned above. “% change from baseline of the primary endpoint and all secondary clinical findings at 16w” will be referred to as the dependent variable, whereas “baseline level of each potential proteomic marker” will be referred to as the independent variable. Then, we will perform the same statistical analysis as described above.

### Development of a score for evaluating disease activity in AD

3.3

Since measuring disease activity is an important component of AD management, biomarkers that capture the complex and heterogeneous biology of AD may have the potential to complement clinical disease activity assessment. We hypothesize that the measurement of multiple biomarkers and potential proteomic markers combined into a more limited score could quantitatively and objectively characterize AD activity and enhance AD activity assessment. Thus, after evaluating the associations of biomarkers and potential proteomic markers with primary and secondary endpoints, we will investigate the possibility of developing a score for evaluating disease activity in AD.

A score for disease activity in AD will be determined using the values of 18 biomarkers (% eosinophils, LDH, total IgE, soluble IL-2 receptor, CCL17, CCL22, CCL27, CCL18, CCL26, IL-13, IL-22, IL-24, IL-25, IL-31, IL-33, TSLP, periostin, and SCCA2) and potential proteomic markers (of roughly 300 molecules) during the 16w period of dupilumab treatment.

To evaluate the internal consistency of biomarkers and potential proteomic markers, Cronbach's α will be calculated. Mutual correlations of biomarkers and potential proteomic markers will be determined using correlation coefficients.

To explore potential groupings of the biomarkers and potential proteomic markers into a more limited number of score components, factorial analysis based on correlation coefficients will be performed. The selection of the number of score components will be based on the eigenvalues. To understand the meaning of the score components, promax rotation will be used. Finally, analysis of covariance or generalized linear models adjusting for confounding factors such as sex, age, and medical and family history will be used to evaluate the associations of combined scores with the primary endpoint and all secondary endpoints.

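### The Section 3.3 score is meant to measure current AD activity, but it is judged only against 16-week response and combines about 318 markers that the design cannot support

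*Protocol article*

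**What the plan says.** All references are to the Protocol article.

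- **Aim and inputs (Section 3.3).** The score is to quantify AD activity as a complement to clinical assessment. It combines the 18 biomarkers with "potential proteomic markers (of roughly 300 molecules) during the 16w period of dupilumab treatment".
- **Construction (Section 3.3).** Cronbach's alpha is calculated, then a factor analysis of the correlation coefficients with promax rotation. On dimension: "The selection of the number of score components will be based on the eigenvalues". No cut-off is given.
- **Evaluation (Section 3.3).** Analysis of covariance or generalized linear models "will be used to evaluate the associations of combined scores with the primary endpoint and all secondary endpoints".
- **Endpoints (Section 2.6).** The primary and all nine secondary endpoints relate baseline marker levels to % change from baseline at week 16 in EASI, POEM or one of the NRS scales.
- **Sampling (Section 2.5).** EASI, the patient-reported scales and the 18 biomarkers are taken at weeks 0, 2, 4, 8 and 16. Proteomics is run on the patients' "sera on the day that injections of dupilumab start and at 2w of treatment".
- **Numbers (Section 2.3).** The target "was determined based on past experiences and feasibility". It is assumed that "approximately 25% of enrolled patients with dupilumab treatment will discontinue the treatment", and "a plan was set to enroll more than 130 subjects and perform data analysis of at least 100 subjects".

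**The concern.** Three things fixed in Section 3.3 do not fit together.

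1. **Purpose and criterion differ.** An activity measure should track how severe the disease is when the sample is taken. The endpoints ask how much the patient improves by week 16. A marker can follow current severity closely and say nothing about later response, or the reverse. Neither a strong nor a weak association with % change would therefore show whether the score measures activity. If on-treatment values enter the score, it is not a baseline predictor either, although Section 2.6 defines every predictor as a baseline level.
2. **Inputs and schedule differ.** The score is described as one instrument over 16 weeks, but most of its items exist at only two of the five visits.
3. **There are more variables than observations.** A factor analysis of a singular correlation matrix is poorly determined. A loosely specified eigenvalue rule can then keep many components that are only sampling noise.

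At stake is whether the final step can support a claim that the score measures AD activity.

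**Working it through.** **Number of patients.** The plan's own figure comes first: 130 × (1 − 0.25) = 97.5, against the stated minimum of 100 analysed. In the other direction, 100 / 0.75 = 133.3, so 134, which agrees with enrolling more than 130. The planned numbers are consistent. About 98 to 100 patients would have week-16 data. The factor analysis itself needs no week-16 outcome, so about 130 could enter at baseline.

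**Number of variables.** 18 + about 300 = about 318. This assumes that all the proteins enter and that none duplicates one of the 18.

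**Rank.** A correlation matrix from n rows has rank at most n − 1. For 318 variables:

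| Rows | Source | n/p | Maximum rank | Zero eigenvalues (at least) |
|---|---|---|---|---|
| 98 | completers, one visit | 0.31 | 97 | 221 |
| 130 | all enrolled, baseline | 0.41 | 129 | 189 |
| 196 | 98 patients × 2 visits | 0.62 | 195 | 123 |
| 260 | 130 patients × 2 visits | 0.82 | 259 | 59 |

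The matrix is singular in every row. Even complete overlap of the 18 with the proteins would leave about 300 variables, still more than 260 rows. The 18 biomarkers alone give n/p = 98/18 = 5.4 and full rank.

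**What an eigenvalue rule would keep.** The above-1 cut-off is assumed here. Means of 40 simulated sets of independent normal variables:

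| Rows × variables | Eigenvalues above 1 | Largest eigenvalue |
|---|---|---|
| 98 × 318 | 90.9 | 7.6 |
| 130 × 318 | 101.7 | 6.4 |
| 260 × 318 | 120.6 | 4.3 |
| 98 × 18 | 8.1 | 1.9 |

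The last line shows that a fixed cut-off of 1 is unsafe even for the 18 biomarkers. The rank limit does not depend on any cut-off.

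**Cronbach's alpha.** Standardised alpha = p·r / (1 + (p − 1)·r), with mean inter-item correlation r. At an assumed r = 0.02:

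- 318 items: 6.36 / 7.34 = 0.87
- 18 items: 0.36 / 1.34 = 0.27

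With 318 items, a very small mean correlation already gives a high value.

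**Criterion and visits side by side.**

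| | Weeks available |
|---|---|
| EASI | 0, 2, 4, 8, 16 |
| 18 biomarkers | 0, 2, 4, 8, 16 |
| Proteins | 0, 2 |
| Outcome used to judge the score | % change from week 0 to week 16 only |

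Same-visit EASI exists wherever the score can be computed, but Section 3.3 does not name it as a criterion. A score with proteins has no value at weeks 4, 8 and 16.

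**The case against.** The strongest reply is that this is an exploratory score in an exploratory study, described in a condensed article, and that validation detail belongs in the full protocol or analysis plan. Much of that stands: the absence of a cross-validation plan or an eigenvalue cut-off is not in itself a fault. What remains is what the article does fix, namely the inputs, the method and the criterion.

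Weeks 0 and 2 do lie within the 16-week period, so the wording on proteins can be read as loose rather than contradictory. Even so, the two marker sets cover different visits and are treated as one. The proteomic markers might also be a preselected subset, but Section 3.3 gives the count as about 300 and states no selection step. Relating the change in a score to % change in EASI would be a fair check of responsiveness, but the text does not say that a change in score is meant.

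A reader might infer more than the document supports:

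- **That the fit will be optimistic because the score is built and tested in the same patients.** Factor analysis of correlations does not use EASI. With pure noise at 98 × 318, the first component was significant at 5% against a null outcome in 4% of 1,000 simulated runs. A null R-squared of 0.30 or 0.43 arises if the best 5 or 10 of 318 markers are picked by outcome, and Section 3.3 states no such step. The null value of 20/97 = 0.21 needs 20 components entered jointly, a number the document does not give.
- **That alpha will look excellent whatever the markers measure.** For 318 independent noise items at n = 98, simulated alpha averages about 0 (5th to 95th percentile −0.25 to 0.22). The 0.87 depends on the assumed r = 0.02.
- **That only 98 patients are available throughout.** At baseline it can be about 130.

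**Conclusion.** The point holds in this form. The main defect is the criterion: a score intended to measure current activity is evaluated clinically only against 16-week response, although EASI is collected at every visit where the biomarkers are. This needs no simulation and no assumption beyond the text.

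Two supporting defects also stand. No protein-containing score can exist at three of the five visits. And about 318 variables exceed the available rows under every reading examined, from 98 to 260, so the correlation matrix is singular. The figures of about 91 (n = 98) and 102 (n = 130) retained noise components rest on an assumed eigenvalue-above-1 rule. The count of 318 assumes that all the proteins enter without overlap.

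The consequence is confined to the exploratory score. The primary endpoint, the nine secondary endpoints and the sample size are not affected.

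**What to change.** 1. Build the 0-16 week activity score from the 18 biomarkers. Restrict any protein-containing score to weeks 0 and 2, and reword Section 3.3 to agree with Section 2.5.
2. Evaluate the activity score against EASI at the same visit, in a mixed model with a patient random intercept. For % change at week 16, use a separate score built from baseline values only.
3. Choose the number of components by parallel analysis rather than a fixed eigenvalue cut-off. This still fits the present wording, since it is itself based on eigenvalues.
4. If any markers or components are selected or weighted using the outcome, repeat that step inside cross-validation and report the cross-validated fit. A purely outcome-blind factor score does not need this.
5. Do not rely on Cronbach's alpha over all 318 variables.

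The cost is wording and some extra programming, with no new patients, visits or assays. The downside is that there is no protein score after week 2.

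### Cronbach's α is planned on the marker pool and not within the score components, so a high value would not show that the markers form one scale

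*Protocol article*

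**What the plan says.** Section 3.3 (development of a disease-activity score) lists its steps as follows.

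- **Items.** "A score for disease activity in AD will be determined using the values of 18 biomarkers" together with "potential proteomic markers (of roughly 300 molecules) during the 16w period of dupilumab treatment".
- **Internal consistency.** "To evaluate the internal consistency of biomarkers and potential proteomic markers, Cronbach's α will be calculated". No subset, component, threshold or form of α (raw or standardised) is named.
- **Correlations.** Mutual correlations among the markers come next.
- **Grouping.** "To explore potential groupings of the biomarkers and potential proteomic markers into a more limited number of score components, factorial analysis based on correlation coefficients" is planned. The number of components is set by the eigenvalues, and promax rotation is used to interpret them.
- **Use of the score.** The combined scores are then related to the endpoints by analysis of covariance or generalized linear models.

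No α is mentioned for the components that the factor analysis produces.

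**The concern.** Cronbach's α can be read as internal consistency when the items are meant to reflect one underlying quantity. Section 3.3 does not expect that of its markers. It describes the biology as heterogeneous, and it plans a rotated factor analysis to find several components. A one-dimension index is thus attached to a pool that the plan itself treats as multi-dimensional, and it is absent from the components, where it would have a clear meaning.

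The number of items makes this matter. α rises with item count at a fixed mean correlation, and about 318 items is far more than α is normally asked to summarise. A value that most readers would call excellent could appear for markers that fall into many unrelated groups. α is the only quantity that the section labels as internal consistency, so a high pooled figure could later be cited as support for combining the markers, which it cannot supply.

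**Working it through.** The article states no α and no correlation among markers, so there is no figure of the plan's own to reproduce. The question is what α can and cannot show at the plan's item counts.

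**Inputs from the document**
- 18 named biomarkers (sections 2.5 and 3.3).
- About 300 proteins (section 2.5: "We also perform proteomic analysis (of roughly 300 proteins"; repeated in section 3.3).
- Pooled item count k = 18 + 300 = 318, approximately.

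**Assumed inputs**
- Mean inter-marker correlation r from 0.01 to 0.10.
- Correlation within a related group of markers 0.3, and zero between groups.

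**Formula.** Standardised α = k·r / (1 + (k − 1)·r), where r is the mean inter-item correlation.

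**Step 1: effect of item count.** For k = 318 and r = 0.03: 318 × 0.03 / (1 + 317 × 0.03) = 9.54 / 10.51 = 0.91.

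| Mean r | α, k = 18 | α, k = 300 | α, k = 318 |
|---|---|---|---|
| 0.01 | 0.15 | 0.75 | 0.76 |
| 0.03 | 0.36 | 0.90 | 0.91 |
| 0.05 | 0.49 | 0.94 | 0.94 |
| 0.10 | 0.67 | 0.97 | 0.97 |

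Solving for the mean correlation that gives α = 0.90: r = 0.9 / (k − 0.9(k − 1)). For k = 318 this is 0.9 / 32.7 = 0.0275; for k = 300 it is 0.0291; for k = 18 it is 0.9 / 2.7 = 0.333.

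**Step 2: markers that do not belong together.** Split 318 markers into ten mutually uncorrelated groups (eight of 32, two of 31), with correlation 0.3 inside each group.
- Mean r = 0.3 × (8 × 32 × 31 + 2 × 31 × 30) / (318 × 317) = 0.3 × 9,796 / 100,806 = 0.0292.
- α = 318 × 0.0292 / (1 + 317 × 0.0292) = 0.905 (unrounded r used).
- Five such groups give 0.95, and twenty give 0.82.

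**Step 3: proteins alone.** Ten uncorrelated groups of 30 give mean r = 0.3 × 8,700 / 89,700 = 0.0291 and α = 300 × 0.0291 / (1 + 299 × 0.0291) = 0.90. Splitting the pool into the two marker sets therefore does not remove the problem for the proteins.

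**Step 4: limits in the other direction.**
- 318 fully independent markers, simulated with 100 patients: median α −0.03, 5th to 95th percentile −0.27 to 0.18.
- One common factor with loadings of equal size (correlations ±0.3) and half the markers moving the opposite way: α = −0.43. With 40% moving the opposite way: 0.78.

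So pooled α can be high, low or negative, depending on features that have little to do with whether the markers form one scale.

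**Step 5: α within components.** Under the ten-group assumption, a component of 32 markers has α = 32 × 0.3 / (1 + 31 × 0.3) = 9.6 / 10.3 = 0.93, against 0.905 pooled. For the 18 biomarkers in three uncorrelated groups of six, it is 6 × 0.3 / (1 + 5 × 0.3) = 0.72 within a group, against 0.635 pooled. The pooled figure does not distinguish ten unrelated groups from one scale; the per-component figure refers to items that have been grouped.

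**The case against.** The sentence does not say that a single α is taken over all 318 markers. A separate α for each set is possible, and for the 18 biomarkers alone α = 0.90 would need a mean correlation of 0.333, so item-count inflation largely disappears there. This stands for the 18. It does not rescue the set of about 300 proteins (Step 3), and in neither case is α planned on the components.

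The order of the steps is also inferred from the order of the sentences. The point does not rest on order, since no per-component α is written anywhere in the section.

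The weightiest objection concerns consequence. No threshold is set for α and no decision uses it: eigenvalues set the number of components, the factor analysis forms them, and regression models test the scores. The mutual correlations planned alongside would help to expose a misleading α. The section only explores whether a score is feasible. All of this stands, and it keeps the point small.

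Three stronger readings are tempting, and the document does not support them.

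- **Measurement units distort α.** The items do mix scales ("18 biomarkers including % eosinophils in blood cell count, LDH, total IgE, soluble interleukin 2 receptor"), and the log transformation is stated only for clinical scores ("The primary EASI and all secondary subjective scores will be logarithmically transformed"). But units affect only raw α. The article does not say that raw α is meant, the neighbouring steps work from correlations, and a condensed article may leave this detail to the full plan. Unequal units would also pull raw α down, so they cannot explain a falsely high value.
- **α will come out high.** Step 4 shows that it need not.
- **Conclusions about the score would be invalid.** α is planned for the markers, not for the score, and no stated conclusion rests on it.

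**Conclusion.** The point holds as a low-severity, inexpensive improvement. Section 3.3 states a statistic and the items it covers, and those are the wrong items for the purpose: a pool expected to contain several dimensions, and not the components derived from it. With about 300 or more items, α could be about 0.90 or higher at a mean correlation near 0.03, or with ten unrelated groups of markers, so a high value would not show that the markers form one scale. A low or negative value would be equally hard to interpret.

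These sizes rest on assumed correlations and on standardised α. The formula and the item counts do not depend on those assumptions; how large α would actually be does. The harm is limited to a misleading reported figure in an exploratory part of the study. The analyses of individual markers in sections 3.1 and 3.2 do not use α and are not affected.

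**What to change.** Replace the α sentence in section 3.3 with wording to this effect, placed after the factor analysis:

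> Once the score components have been selected, internal consistency will be described separately within each component by standardised Cronbach's α, computed on transformed markers with negatively loading markers reversed, and reported with the mean inter-item correlation and the number of markers. An α for the pooled markers will not be interpreted as evidence that they can be combined.

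The cost is a little more analysis work and no new data. Two limits should be stated with the result. The components are chosen on the same data, so α within them will be somewhat optimistic. It also still depends on item count: a component of 32 markers at an assumed correlation of 0.3 already gives 0.93. That is why the mean correlation and the number of markers belong beside it, and why the result should be described as exploratory.
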